## Abstract

**Background:**

Neoadjuvant chemoradiotherapy has become the standard treatment for mid-to-low location LARC. Recently, total neoadjuvant therapy (TNT) has been used in patients with ‘high-risk’ or ‘very high-risk’ LARC according to ESMO guideline (2017). TNT not only increases the pathological complete response (pCR) rate, but also provides patients with more opportunities to preserve organ function. However, TNT mode seems to have reached a plateau. Some clinical studies published in recent years have also confirmed that different modes of neoadjuvant chemoradiotherapy combined with ICIs can further improve the pCR rate to varying degrees. It is necessary to explore an appropriate treatment mode for patients with mid-to-low location, who are unresectable or difficult to achieve R0 resection at the initial stage of surgery and have a strong desire to preserve anal cavity. Numerous basic researches have demonstrated that radiotherapy can remodel the tumor immune microenvironment and play a potential synergistic effect on ICIs. Therefore, this study will aim to explore whether TNT combined with ICIs could improve pCR rates in patients with ‘high-risk’ or ‘very high-risk’ LARC.

**Methods:**

This prospective, single-center, single-arm phase II trial aims to assess the pCR rate of neoadjuvant long-course concurrent chemoradiotherapy sequential 6 cycles CapeOX regimen combined with sintilimab in ‘high-risk/very high-risk’ LARC patients with mid-to-low location and with pMMR phenotype. The primary endpoint for this study is the pCR rate. Secondary endpoints include 2-year sustained of clinical complete response (cCR) rate; CR rate (the rate of patients with sustained cCR for 2 years and pCR); major pathological remission; neoadjuvant rectal score; 3-year non-regrowth disease free survival; 3-year disease-free survival; 3-year overall survival; 3-year localized recurrence-free survival; 3-year distant metastasis free survival; 3-year stoma-free survival, anal sphincter preservation rate; surgical R0 resection rate and safety (adverse events during neoadjuvant therapy and 30 days after surgery, as well as tolerance).

**Discussion:**

This study will investigate whether neoadjuvant long-course concurrent chemoradiotherapy sequential total neoadjuvant chemotherapy combined with immunotherapy could further enhances tumor pCR rate in ‘high-risk/very high-risk’ LARC patients with mid-to-low location and with pMMR phenotype and is expected to improve prognosis.

**Trial registration:**

ClinicalTrials.gov NCT05998122.

## Background

Among all cancers, colorectal cancer ranks third in incidence and second in mortality worldwide (1). In China, the incidence of rectal cancer is on the rise, and most patients are diagnosed with locally advanced rectal cancer (LARC) at initial diagnosis (2), characterized by low rates of R0 resection and anal preservation (3). Preoperative neoadjuvant chemoradiotherapy (nCRT) has emerged as the standard treatment for mid-to-low location LARC (4). Statistical data indicates that nCRT achieves pathological complete response (pCR) rate of 8% - 24%, offering patients who achieved clinical complete response (cCR) potential ‘Watch and Wait’ opportunities (5–8). Preserving anal sphincter function while maintaining efficacy has become a key issue for LARC. Clinical trials demonstrate that total neoadjuvant therapy (TNT) can improve both pCR rates and organ preservation. However, in most trials, the pCR rate related to TNT was still lower than 30%, highlighting the need for novel strategies to enhance tumor response (9). The European Society for Medical Oncology (ESMO) guideline classify patients into different subgroups based on digital rectal examination (DRE), rectal high-resolution magnetic resonance imaging (HRMRI), and rectal intraluminal ultrasound (10). The guideline recommends adjusting treatment regimens for patients in different risk levels to achieve better efficacy and lower risk in precise treatment. While PD-1/PD-L1 inhibitors revolutionized care of colorectal cancer with deficient mismatch repair (dMMR) or microsatellite instability-high (MSI-H) phenotype, these represent only 8% - 10% of the cases. The remaining cases of proficient mismatch repair (pMMR) or microsatellite stabilization (MSS) phenotype could hardly benefit from immune checkpoint inhibitors (ICIs) treatment. Interestingly, it has been demonstrated that radiotherapy has the effect of stimulating the release of neoantigens and activating immunity (11). Building on this, the VOLTAGE study demonstrated that adding ICIs after nCRT could increase the pCR rate of MSS phenotype rectal cancer to 30% (12). At present, studies have shown that TNT combined with immunotherapy demonstrates better tumor regression and pCR rates, but its survival benefits such as DFS and OS need longer follow-up (13). Crucially, no solid evidence yet confirms whether adding immunotherapy significantly boosts pCR rates for mid-to-low location LARC patients with ‘high-risk/very high-risk’ according to ESMO guideline. Our center conducted a prospective, single-arm, observational study of long course concurrent chemoradiotherapy consolidation chemotherapy combined with PD-1 inhibitors, and the results are being submitted (STARS-RC03, NCT04906044). A total of 29 pMMR LARC patients received neoadjuvant long-course concurrent chemoradiotherapy followed by at least 3 cycles of CapeOX chemotherapy combined with PD-1 inhibitor. One patient discontinued treatment and was not effectively evaluated for efficacy. Our results showed that this regimen was safe and tolerated. Grade III toxicity was mainly associated with chemotherapy-induced hematological toxicity (51.71%, 15/29), and was reversed through active symptomatic treatment. No grade III or higher immunotherapy-related toxicity was observed. The pCR rate was 17.86% (5/28), and the overall complete response rate (cCR and pCR) was 50% (14/28). In 19 patients who undergone radical surgery, the major pathological remission (MPR) rate was 73.58% (14/19), and the R0 resection rate was 89.47% (17/19). Subgroup analysis found that the CR rate was positively correlated with the number of consolidation therapy, but the incidence of grades III or higher adverse events did not increase with the number of consolidation therapy. Building on these results, we propose the hypothesis that neoadjuvant long-course concurrent chemoradiotherapy sequential 6 cycles CapeOX regimen combined with PD-1 inhibitor further enhances the tumor pCR rate and has the potential to improve prognosis in mid-to-low location LARC patients with ‘high-risk/very high-risk’ and with pMMR phenotype.

## Methods and analysis

### Trial organization, ethical approval, and drug supply

The trial is co-sponsored by the Department of Gastric and Colorectal Surgery and the Department of Radiotherapy of the First Hospital of Jilin University. Scientific review was obtained from the Review Board of the First Hospital of Jilin University on August 16, 2023 (2023-HS-084). Ethical approval was obtained from the Ethics Committee (Approval No.23K162-002) of the First Hospital of Jilin University on October 18, 2023. All relevant materials have been registered on the official ClinicalTrials.gov website (NCT05998122). The PD-1 inhibitor selected for this study is sintilimab from Innovent Biologics, Inc.

### Study population

All included patients required pathological immunohistochemical confirmation of rectal adenocarcinoma with intact expressions of all 4 MMR proteins, had mid-to-low location tumors (distal margin ≤10 cm from anal verge) verified by HIMRI, and were risk-stratified according to ESMO rectal cancer guidelines (2017) as ‘high-risk’ (cT3c/d or very low localization levators threatening, MRF-negative cT3c/d mid-rectum, cN1-N2 with extranodal involvement, EMVI-positive, or limited cT4aN0) or ‘very high-risk’ (cT3 with MRF involved, any cT4a/b, or lateral lymph node metastasis) (10). Participants willingly volunteered for this clinical study and provided written informed consent. Detailed inclusion and exclusion criteria are available in **Table 1**. The study commenced in October 2023 and is expected to end before December 2028. If all enrolled patients complete all treatment plans during this period, the study will be terminated. Study enrollment is ongoing, with the first patient recruited on October 31, 2023.

**Table 1 T1:** Patient inclusion and exclusion criteria.

Inclusion criteria:	Exclusion criteria:
1. The patients and their families are able to understand and are willing to participate in this clinical study, and sign an informed consent form; 2. Age: 18~75 years old, no gender limit; 3. Pathologically diagnosed rectal adenocarcinoma: differentiated into Grade 1-3, that is, high, medium, and poorly differentiated tubular adenocarcinoma; classified as pMMR; 4. The initial risk stratification (from Rectal cancer: ESMO Clinical Practice Guidelines, 2017 edition) is as follows: 1) ‘high-risk (Locally Advanced Disease)’: cT3c/d or very low localization levators threatened, MRF clear; cT3c/d mid-rectum, cN1–N2 (extranodal), EMVI+, limited cT4aN0; 2) ‘very high-risk (Advanced disease)’: cT3 with any MRF involved, any cT4a/b, lateral node+; 5. The lower margin of the tumor located within 10cm from the anal margin (including patients with mrLR3 or mrLR4 at initial evaluation); 6. No distant metastasis; 7. ECOG PS score 0-1; 8. Hepatitis B Surface Antigen (HBsAg) (-) and Hepatitis B Core Antibody (HBcAb) (-). If HBsAg (+) or HBcAb (+), hepatitis B virus deoxyribonucleic acid (HBV-DNA) must be less than 1000 copies/mL or 200 IU/mL before entering the group; 9. HCV antibody (-); 10. The main organ function is normal; 11. No history of pelvic radiotherapy; 12. No history of rectal cancer surgery or chemotherapy; 13. Not accompanied by systemic infections requiring antibiotic treatment; 14. Heart, lung, liver, and kidney functions can tolerate surgery; 15. Others, based on the results of previous medical history, vital signs, physical examination or laboratory examination, the research doctor judges that you are suitable for participating in this clinical study.	1. Recurrent rectal cancer; 2. ECOG PS score 2-5; 3. Patients who are planning to undergo or have previously received organ or bone marrow transplantation; 4. Myocardial infarction or poorly controlled arrhythmia (including QTc interval ≥ 450 ms for males and ≥ 470 ms for females) occurred within 6 months before the first medication (QTc interval is calculated by Fridericia formula); 5. Existence of NYHA standard grade III to IV cardiac insufficiency or color Doppler ultrasound examination: LVEF (left ventricular ejection fraction) <50%; 6. Human immunodeficiency virus (HIV) infection; 7. Suffer from active tuberculosis; 8. Past and present patients with interstitial pneumonia, pneumoconiosis, radiation pneumonia, drug-related pneumonia, severely impaired lung function, etc., which may interfere with the detection and treatment of suspected drug-related lung toxicity; 9. Patients with active or suspicious autoimmune disease, or with a history of that; 10. Received treatment with live vaccines within 28 days before the first administration; except for inactivated viral vaccines for seasonal influenza; 11. Have received other antibody/drug treatments against immune checkpoints in the past, such as PD-1, PD-L1, CTLA4, etc.; 12. Known to have a history of severe allergies to any monoclonal antibody or research drug excipients; 13. Patients who have had a malignancy within the past 5 years with a survival rate significantly lower than the Center’s historical data on rectal cancer survival rates (properly treated basal cell carcinoma, squamous skin carcinoma, mini-kidney carcinoma, breast carcinoma, and papillary thyroid carcinoma are not included in this category); 14. The patient has had arterial embolism diseases in the past 6 months, such as angina pectoris, MI, TIA, CVA, etc.; 15. Have received other types of anti-tumor or experimental treatments; 16. The patient is a female during pregnancy or lactation; 17. The patient has other diseases or abnormal mental states, which may affect the patient’s participation in this study; 18. There are patients who may increase the risk of participating in research and research medication, or other severe, acute and chronic diseases, who are not suitable for clinical research based on the judgment of the investigator.

MRF, mesorectal fasciae; EMVI, extramural vascular invasion; ECOG PS score, Eastern Cooperative Oncology Group Performance Status; MI, myocardial infarction; TIA, transient ischemic attack; CVA, Cerebral Vascular Accident.

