### Study endpoints and assessment

The primary endpoint of this trial is the pCR rate, defined as the percentage of patients who achieved pCR after nCRT in the eligible population. Secondary endpoints include 2-year sustained of cCR rate; CR rate (the rate of patients with sustained cCR for 2 years and pCR); MPR, which is defined as residual viable tumor (RVT) ≤10%; neoadjuvant rectal (NAR) score, which were calculated based on pathological and clinical staging (NAR=[5pN - 3(cT - pT) + 12]^2^/9.61); 3-year non⁃regrowth disease free survival; 3-year disease-free survival; 3-year overall survival; 3-year localized recurrence-free survival; 3-year distant metastasis free survival; 3-year stoma-free survival, anal sphincter preservation rate; surgical R0 resection rate and safety (adverse events during neoadjuvant therapy and 30 days after surgery, as well as tolerance). In addition, the study also has exploratory endpoints to further investigate potential factors related to antitumor therapy, such as infiltrating lymphocytes in tumor tissue, the structure of gut microbiome, and RAS/BRAF status.

The per-protocol set (PP) is defined as subjects who strictly adhered to the study protocol without major violations, completed all treatment and follow-up, and had measurable data for the primary endpoint (pCR). The modified intention-to-treat set (mITT) excludes participants who received no intervention or provided absolutely no post-baseline data. Patients achieving cCR who opt for Watch & Wait management are included in the mITT set for efficacy analysis.

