### Follow-up

The follow-up methods include outpatient visits and telephone follow-ups. The follow-up schedule consists of assessments every 3 months for the first 2 years, followed by visits once every 6 months in the 3rd year, and subsequently, visits once every 1 year for the 4th–5th years. Procedure refer to ESMO Rectal Cancer Guidelines (2017) (10). Follow-up evaluations include, but are not limited to DRE, carcinoembryonic antigen measurements, endoscopy and biopsy, abdominal enhanced computed tomography, HRMRI, and anal cavity ultrasound.

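### The termination rule is tied to completing treatment, which as written conflicts with the 2-year and 3-year endpoints and the follow-up schedule

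*Protocol article*

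**What the plan says.** Study population gives the calendar: "The study commenced in October 2023 and is expected to end before December 2028". The closing rule follows directly: "If all enrolled patients complete all treatment plans during this period, the study will be terminated". The same paragraph adds: "Study enrollment is ongoing, with the first patient recruited on October 31, 2023".

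Study endpoints and assessment lists a 2-year sustained-cCR rate and a CR rate that counts pCR together with cCR lasting 2 years. It also lists six rates at 3 years: non-regrowth disease-free survival, "3-year disease-free survival; 3-year overall survival; 3-year localized recurrence-free survival", distant metastasis-free survival and stoma-free survival. Its per-protocol set admits only patients who have finished follow-up as well as treatment.

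Follow-up plans "assessments every 3 months for the first 2 years, followed by visits once every 6 months in the 3rd year", and then "visits once every 1 year for the 4th–5th years".

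**The concern.** The only event that the closing rule names is the end of treatment, and follow-up is not mentioned. Treatment takes under half a year before surgery, whereas eight secondary endpoints (two at 2 years, six at 3 years) need years of observation after it. A study that stops when the last patient finishes treatment cannot deliver those endpoints for patients who entered late.

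The 3-year rates would then be heavily censored, or would rest mainly on early enrollees. Recent Watch-and-Wait patients could not be classified for CR, because their 2-year cCR status would be unknown at closure. The per-protocol set has the same difficulty, since it requires completed follow-up.

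**Working it through.** **Figure not in dispute.** The sample size reproduces with the normal approximation for one proportion: n = [(1.96·√(0.16·0.84) + 0.842·√(0.36·0.64)) / 0.20]² = 31.5, rounded up to 32, and 32/0.8 = 40. It concerns pCR only and does not depend on when the study closes.

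**Time on neoadjuvant treatment.** Study design gives 5 weeks of chemoradiotherapy, a gap of 7-10 days, then 6 cycles. The cycle length is not stated; I assume 21 days and show 14 to 28 as the range.
- 21-day cycles: 35 + (7 to 10) + 126 = 168 to 171 days, or 24.0 to 24.4 weeks (about 5.6 months at the upper end).
- 14- to 28-day cycles: 126 to 213 days, or 18 to 30 weeks.

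**Closure under the written rule.** Let accrual last A months, let a patient enrol e months into it, and let s be the interval from the end of neoadjuvant therapy to surgery. The article does not give s; I assume 0 to 12 weeks, i.e. 0 to 2.8 months. At closure:
- time since enrolment = (A − e) + 5.6 + s
- time since end of neoadjuvant therapy = (A − e) + s

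For the last patient, e = A. That leaves 5.6 + s months from enrolment and s months from the end of neoadjuvant therapy, whatever the accrual pace.

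For the first patient, e = 0. Reaching 36 months from enrolment needs A ≥ 36 − 5.6 − s, i.e. 27.6 to 30.4 months of accrual. Reaching 24 months from the end of neoadjuvant therapy needs A ≥ 24 − s, i.e. 21.2 to 24 months.

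**The expected end date taken alone.** From 31 October 2023 to 30 November 2028 is 61.0 months. Counting back from 30 November 2028, and using 171 days where the clock starts at the end of neoadjuvant therapy:

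| Needed | Clock starts at | Latest enrolment | Accrual available |
|---|---|---|---|
| 3 years | enrolment | 30 Nov 2025 | 25.0 months |
| 3 years | end of neoadjuvant therapy | 12 Jun 2025 | 19.4 months |
| 2-year cCR | end of neoadjuvant therapy | 12 Jun 2026 | 31.4 months |
| 5 years | enrolment | 30 Nov 2023 | 1 month |
| 5 years | end of neoadjuvant therapy | 12 Jun 2023 | none (before the first patient) |

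Adding 4 to 12 weeks for assessment moves the 2-year date to between mid-May and mid-March 2026. On the last row, the first patient would end neoadjuvant therapy in April 2024 and reach 5 years in April 2029. With 14-day cycles the latest enrolment on that row would be 27 July 2023, so still nobody qualifies.

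**Two constraints compared.** If accrual were short enough for the date to give everyone 3 years from enrolment (25.0 months or less), the written rule would close the study no later than 25.0 + 5.6 + 2.8 = 33.4 months after the first enrolment. Nobody would then have 36 months. The closing rule, more than the date, is what threatens the endpoints.

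**The case against.** The strongest reply is that the literal reading is the least coherent one. A 61-month window makes little sense for about 24 weeks of treatment, but it suits accrual plus roughly 3 years of follow-up. The article has a visit schedule, keeps patients who stop treatment early under follow-up, and requires completed follow-up for the per-protocol set. On this view the phrase about treatment plans is loose and was meant to cover follow-up.

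That is a fair account of probable intent, and nothing suggests that the sponsor chose to forgo follow-up. It does not rescue the sentence. The per-protocol definition names treatment and follow-up as separate things. The section on discontinuing or modifying interventions uses treatment plan for what the MDT decides next, and mentions follow-up in addition. A reader applying the rule has no textual basis for including follow-up.

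Three further points stand. Closure is triggered only when all enrolled patients have finished treatment, so with long accrual early enrollees would already have accumulated follow-up. Administrative censoring is ordinary in time-to-event analysis and does not by itself invalidate a 3-year estimate, though precision depends on how many remain at risk. And no listed endpoint is measured at 5 years, so the mismatch with the year 4-5 visits costs no endpoint.

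**Conclusion.** The contradiction is real and is in stated text, so it is not detail that an article may leave to the full protocol. Followed as written, the closing rule conflicts with the 2-year sustained-cCR and CR endpoints, the six 3-year endpoints and the follow-up schedule. The last enrollee would have about 24 weeks plus any interval to surgery from enrolment, and the loss falls mainly on later enrollees. How many patients are affected depends on the accrual length, which the article does not give.

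A reader might infer more: that the study stops before December 2028 in any event, and that this date cuts off the 2-year and 3-year endpoints. The documents do not support that. The text says only that the study "is expected to end before December 2028", which is an expectation and not a cap. The date also leaves 19 to 25 months of accrual for the 3-year endpoints and about 31 months for 2-year cCR, and no passage says that accrual of the 40 patients runs longer. The date conflicts outright only with the year 4-5 visits. Those fit patients enrolled by 30 November 2023 if counted from enrolment, and nobody if counted from the end of neoadjuvant therapy.

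These dates assume 21-day cycles and a study end of 30 November 2028. The primary endpoint and N = 40 are unaffected. The point should be corrected, but it does not threaten the main result.

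**What to change.** Replace the termination sentence with a rule based on follow-up, for instance: *The study ends when the last enrolled patient has completed the follow-up needed for the 3-year endpoints and the last Watch-and-Wait patient has completed the 2-year sustained-cCR period, or has died or withdrawn.* Count both periods from the time origins used in the endpoint definitions. The choice matters: moving the 3-year clock from enrolment to the end of neoadjuvant therapy shifts the latest workable enrolment date by about 5.6 months.

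Then align the expected end date with that rule. Reconcile the year 4-5 visits with it too, since a close at 3 years would still truncate them for late enrollees. The protocol should say whether those visits belong to the study or continue outside it.

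The cost is protocol and registry wording and possibly a later formal close-out. The follow-up visits are already scheduled, and neither the treatment, the pCR analysis nor the sample size changes.

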### Study design

This prospective, single-center, single-arm phase II trial aims to assess the pCR rate of neoadjuvant long-course concurrent chemoradiotherapy sequential 6 cycles CapeOX regimen combined with sintilimab in mid-to-low location LARC with ‘high-risk/very-high-risk’ and with pMMR phenotype. The treatment process is showed in **Figure 1**. Enrolled patients will initially undergo long-course concurrent chemoradiotherapy, targeting the primary tumor area and regional lymphatic drainage area: 50 Gy/25 fractions/5 weeks with intensity-modulated radiation therapy or volumetric modulated arc therapy, alongside simultaneous capecitabine 825 mg/m^2^, twice daily, throughout the radiotherapy period. Following the completion of neoadjuvant concurrent chemoradiotherapy (7–10 days later), the subjects will receive 6 cycles of CapeOX combined with sintilimab treatment: sintilimab 200 mg intravenously on the day 1, oxaliplatin 130 mg/m2 intravenously on the day 1, and capecitabine 1000 mg/m^2^ orally twice daily from day 1 to day 14. Efficacy evaluations will occur every three cycles using DRE, HRMRI and endoscopy. Patients with progressive disease (PD) will undergo multidisciplinary team (MDT) discussion for alternative treatment strategies, while those with tumor regression and good tolerance will continue therapy. Patients whose tumors have not completely regressed after 6 cycles of consolidation treatment will directly receive surgical treatment. For patients evaluated as cCR, ‘Watch and Wait’ or surgery can be chosen based on MDT discussion and patient preference. The evaluation criteria of cCR according to ESMO guideline (2017), including no palpable tumor on DRE, no residual tumor or white scar under endoscopy, negative scar biopsy, and no residual tumor or residual fibrosis or residual wall thickening because of edema on HRMRI, and no suspicious lymph nodes on T2-weighted images (10, 14).

